The benefits of tDCS include the flexibility to use it for different activities and exercises (as it presents a mobile characteristic) and the possibility of combining it with other interventions. Spampinato et al. (25) showed that the combination of tDCS with a task using reward characteristics produced neurophysiological modulation of inhibitory networks, and it resulted in enhanced retention of the learned task. Thus, it can be used during fine motor tasks [to reinforce learning of coordinative tasks; (26)], global movements [to increase range of movement; (22)] and physical activities [in order to facilitate motor activities; (12)], and to improve heart and autonomic conditions (27).

Some studies have produced positive results when combining VR and tDCS therapies in stimulating the lower limbs for gait improvement (12) and balance (28, 29). However, no studies have investigated VR and tDCS interventions using an upper limb motor task, which might benefit different clinical conditions of individuals with CP. We organised a triple-blinded, randomised, and controlled crossover trial to investigate the upper limb motor function of individuals with CP with the aims of (1) investigating the effectiveness of the use of tDCS while performing a non-immersive VR task on upper limb motor function and (2) to analysing the influence of a combined VR and tDCS in upper limb motor function through different functional assessment scales, reaction times, and coincident timing analysis, as well as physiological analyses such as heart rate variability.

We hypothesise that all individuals with CP will show an improvement in performance after practising a non-immersive virtual reality task, with benefits in upper limb functional scales, reaction times and, coincident timing analysis underpinned by an adaptation of autonomic neural physiological control after the protocol, and retention of these variables at the 30-day follow-up. However, such improvement and benefits will be more evident after the application of active tDCS than the sham (placebo) tDCS group. If this hypothesis is confirmed, the results of this study will be relevant to the treatment of individuals with CP.

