### Overview of the Study Design

A triple-blinded randomised controlled crossover trial with a 1:1 allocation ratio will be conducted, and all participants will undertake non-immersive VR tasks and active or sham tDCS. Groups A–S will start with 10 daily sessions of tDCS-active combined with VR tasks for 20 min. After a 1 month washout, this group will be reallocated to another 10 daily sessions of 20 min with sham tDCS combined with VR tasks. Meanwhile, groups S–A will carry out the opposite protocol (participants will start an allocated 10 sessions of sham tDCS combined with VR tasks, and after a 1 month washout period will be reallocated to 10 sessions of active tDCS combined with VR tasks). The 1 month washout period has been used and was shown to be sufficient to reset the effects of the first 10 sessions in Biabani et al. (31). Figure 2 summarises the planned experimental design. This research protocol follows the SPIRIT recommendations.

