### Assessments for Primary Outcome

The VR task will be used to assess the participants' motor abilities (accuracy, precision, and trend of anticipation or delay in movement) during each intervention. Also, we will use coincident timing and reaction time tasks, ABILHAND-Kids, ACTIVLIM-CP, and visual and cognitive assessments to characterise the group and to find influences on motor improvement by using correlation tests. These tests will be carried out at three stages: initial assessment (D0); assessment after five interventions (D5) and final assessment (D11) (Figure 1).

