## Statistical Analysis

For the coincident timing task for the inferential analysis of the initial tasks (transversal) and the longitudinal protocol with tDCS and HRV as dependent variables, the error measures (constant, absolute, and variable errors) will be considered (time in milliseconds). If the data meet the assumptions for the use of parametric analysis, ANOVA will be performed to identify intra and inter-group differences. These, if any, will be detected by the *post hoc* Tukey-HSD test. If the normality assumptions are not met, non-parametric analyses will be undertaken to identify and locate the differences: a Friedman and *post hoc* Wilcoxon test (for within groups) and a Kruskal–Wallis and *post hoc* Mann–Whitney *U*-test (between groups). For the between-groups analysis of HRV indices, MANOVA will be used, with repeated measures for within groups analyses (for evaluations and follow-up) or Mann–Whitney for intergroup analyses and Friedman for intragroup analyses. A significance level of 0.05 (5%) will be defined; all intervals constructed throughout the work will be 95% statistical confidence. The statistical program used will be SPSS (Statistical Package for Social Sciences), version 26.0.

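### For the coincident-timing errors, only the parametric route names a multiplicity-controlled post hoc test; if more than three levels enter the Friedman test, the Wilcoxon fallback lets false differences through at about 12% to 30%

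*Protocol article*

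**What the plan says.** The Statistical Analysis section gives the coincident-timing error measures (constant, absolute and variable error) two routes.

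- Parametric: ANOVA, and for any differences, "These, if any, will be detected by the *post hoc* Tukey-HSD test".
- Fallback: "If the normality assumptions are not met, non-parametric analyses will be undertaken to identify and locate the differences". Within groups this means "a Friedman and *post hoc* Wilcoxon test (for within groups"; between groups, "a Kruskal–Wallis and *post hoc* Mann–Whitney *U*-test (between groups".

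One level covers both routes: "A significance level of 0.05 (5%) will be defined". No adjustment is named for the fallback pairwise tests, and the section does not say which visits or conditions enter the Friedman test.

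Other sections bear on the number of levels. Overview of the Study Design: "A triple-blinded randomised controlled crossover trial with a 1:1 allocation ratio will be conducted". Assessments for Primary Outcome: "These tests will be carried out at three stages: initial assessment (D0); assessment after five interventions (D5) and final assessment (D11". The Introduction also expects retention at a 30-day follow-up, and the Discussion mentions follow-up at 15 and 30 days. On the expected course, the Introduction states that "all individuals with CP will show an improvement in performance after practising a non-immersive virtual reality task".

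**The concern.** Tukey-HSD controls the error rate over all pairs of levels at once. A set of pairwise Wilcoxon tests, each at 0.05, does not. The only safeguard in the fallback is the Friedman test in front of it, and that protects only when all levels are truly equal. Here they are expected to differ, because every child should improve with practice under sham as well as active stimulation. Practice alone can therefore open the gate, after which each remaining null pair is tested at the full 0.05.

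Two things are at stake. The same data would be held to a different error standard depending on a normality check. And within a single error measure, a practice effect with no stimulation effect could produce a spurious difference between visits or, if both conditions enter the test, between active and sham. The fallback is a realistic route, since absolute and variable timing errors are bounded at zero and tend to be skewed.

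**Working it through.** The article gives no family-wise error figure, so there is none to reproduce.

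**Inputs from the article:** alpha 0.05 (taken as two-sided); three assessments per period; two periods; two randomised sequences; 28 participants needed (14 per group), 36 recruited.

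**Assumptions, not in the article:** practice gains of about 0.5 to 1.2 SD; correlation 0.5 between a child's visits; no stimulation effect.

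**Step 1. Number of pairs.** With k levels there are k(k-1)/2 pairs: 3 for k = 3, 6 for k = 4, 10 for k = 5, and 15 for k = 6 (three visits in each of two conditions).

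**Step 2. Approximation once the gate is open.** If m levels are truly equal, the chance that at least one of their pairs is significant at 0.05 is roughly P(range of m standard normals > 1.96 × √2).

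- m = 2: 5%
- m = 3: 12.2%
- m = 4: 20.3%
- m = 5: 28.6%

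For three active-sham pairs at matched visits, no level is shared between pairs, so the chance is 1 - 0.95³ = 14.3%.

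**Step 3. Simulation.** Friedman at 0.05, then Wilcoxon at 0.05 on the truly equal pairs. There were 20,000 runs per case, with n = 14, 28 and 36 and with normal and exponential errors.

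| Layout | Null pairs | At least one false difference |
|---|---|---|
| 3 levels, all equal | 3 | 4.2-4.5% |
| 3 levels, only D0 differs | 1 | 4.6-5.2% |
| 4 levels, only D0 differs | 3 | 11.5-12.5% |
| 5 levels, only D0 differs | 6 | 20-22% |
| 6 cells, same practice curve in both conditions | 3 | 13.4-14.5% |
| 6 cells, both D0s differ | 7 | 24-25% |
| 6 visits, only the first D0 differs | 10 | 29-31% |
| 6 levels, all equal | 15 | 4.4-5.0% |

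The shifts were 1.5 within-child SD where D0 differs, and steps of 1 within-child SD for the practice curve. At correlation 0.5, one within-child SD is √0.5 = 0.71 of the total SD, so 1.5 corresponds to about 1.06 SD.

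A second set (3,000 trials per case, correlation 0.5, n = 14, 18 and 28) used smaller gains. Six cells with means 0, 0.5 and 0.8 SD in both conditions gave 12.9-13.9%, with the Friedman test significant in 83-99% of trials. Six visits with one gain of 0.8 or 1.2 SD and then a plateau gave 26-32%. Three visits gave 4.2-5.1%.

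The results agree across the two sets because, once the Friedman test nearly always rejects, the error depends on the number and arrangement of null pairs and hardly on the size of the gain.

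**Step 4. Between groups.** Two sequences give one pair. Kruskal-Wallis and Mann-Whitney are then the same test, and the post hoc step adds no error.

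**Step 5. With adjustment.** Bonferroni over all pairs in the family brought every simulated layout to about 0.3-2.7%. Holm (n = 18 and 28, correlation 0.5) brought the three-level, four-level and two six-level cases to 1-4%.

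**The case against.** The strongest reply is that the only layout the article spells out is three assessments, D0, D5 and D11. For three levels the Friedman gate holds the error near 5%. A reader might infer that 13% to 30% is a property of the plan; the article does not support that, because the Statistical Analysis section never says that both periods, or follow-up visits, enter one Friedman test. It labels Friedman and Wilcoxon as within-group tests, so routing active versus sham through them is an assumption too. This stands, and the figures must be read as conditional. The condition is nevertheless likely. In a crossover, active versus sham is a within-child contrast, and Friedman with Wilcoxon is the only within-child procedure named for these measures in the fallback. Even one added follow-up visit makes four levels.

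The upper figure is also open to challenge. It needs one early gain and then exactly equal means over five visits. Continued learning, or a reset after washout, would remove several of the null pairs. It is close to worst case and concerns visit pairs, not active versus sham. For active versus sham the figure is 13-14%, and one of the three tests behind it is a baseline comparison.

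Three wider readings are tempting and fail:

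- That the Mann-Whitney step is inflated as well. With two sequences there is only one pair. Repeating the test over visits raises error, but that is a separate matter from the post hoc step.
- That every outcome is affected. The post hoc Wilcoxon is named for the coincident-timing errors. HRV has its own fallback, Friedman within and Mann-Whitney between groups, with no post hoc Wilcoxon.
- That the plan declares its tests unadjusted. It does not use the word, and an adjustment could stand in an analysis plan that is not shown. But the article goes as far as naming the post hoc procedure on each route, controlled on one and plain pairwise on the other. A reader following it literally would run Wilcoxon tests at 0.05.

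**Conclusion.** The point holds in a limited form. As written, the coincident-timing errors have a multiplicity-controlled post hoc procedure only when parametric assumptions are met. The Wilcoxon fallback relies on the Friedman gate, which is adequate for exactly three levels (about 5%) and inadequate beyond that when practice makes the overall test reject. Under the assumed gains and correlation, the chance of at least one false difference per error measure is about 12% with four levels, 13-14% for active-sham pairs in six cells, and up to about 30% on a six-visit plateau. Against the stated 0.05 that is roughly 2.4 to 6 times (0.12/0.05 = 2.4; 0.30/0.05 = 6). The result rests on two things that the article leaves open: the levels in the Friedman test and the size of the practice gain. It is a cheap inconsistency to remove and does not by itself call the design into question.

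**What to change.** In the Statistical Analysis section, state which visits and which conditions form the Friedman family for each coincident-timing error measure, and state that the post hoc Wilcoxon p-values are Holm-adjusted across all pairs in that family. Both routes then aim at the same family-wise standard. The Mann-Whitney comparison needs no post hoc adjustment, because there is only one pair of sequences.

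The cost is a sentence or two of text and some power per pair in the fallback. That loss grows with the family: the smallest p-value is compared with 0.05/3 = 0.0167 for three levels, 0.05/6 = 0.0083 for four and 0.05/15 = 0.0033 for six. This is a reason to keep the family to the visits and conditions the trial means to interpret.

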## Discussion

Although treatment with tDCS is feasible and effective, further studies with individuals with CP are essential for a better understanding of the motor and autonomic effects of treatment with VR associated with tDCS for clinical practice. Therefore, we organised this study to analyse the influence of combined therapy of VR and tDCS for children and adolescents with CP, with VR tasks for upper limb and trunk movements. As outcome measures, we chose different upper limb functional assessment scales, computer tasks for the analysis of reaction time and anticipatory timing, as well as physiological analyses such as heart rate variability (HRV). Considering our hypothesis, supported by previous studies using similar tasks (8, 68, 70, 71), we speculate that all individuals with CP will show an improvement in performance during therapy sections and will maintain this improvement in follow-up assessments (15 and 30 days). We also hypothesise that the individuals using active tDCS with present better results.

The results from this study can positively influence the rehabilitation programs and provide answers to four important topics:

Safety. The tDCS and VR are safe non-invasive techniques according to current knowledge (24, 82). Two systematic reviews of tDCS in children with CP (83) and paediatric motor disorders (22) found that a large number of individuals have been involved in studies with tDCS since 2014 and noted a small number of adverse effects such as erythematous rash, mild skin burn, redness, and tingling of the skin. The use of Virtual reality presented some adverse symptomatology (especially with immersive VR and commercial games) such as nausea, dizziness, disorientation, frustration for the failure of the interface to detect movement or actions, and difficulty with hand-held interfaces, mainly in positioning users with movement and postural impairments (84). Thus, to avoid adverse effects and risks to the individual, the tDCS parameters used in the present trial will be within the safety limits described in the methods, and to prevent the adverse VR effects, we will use a game developed especially for individuals with disabilities with the use of non-immersive VR task.Use of non-commercial games. Despite promising studies in the literature using commercial games (85), an important question is the potential and future use of customised serious games–defined as a game developed for a specific target (84). Commercial games are designed for entertainment rather than rehabilitation and require high cognitive and motor performance, which makes them unsuitable for patients with restrictions on mobility. In contrast, studies using games specifically developed for rehabilitation have presented interesting results (71). Thus, for the present study, we selected a serious game that provided an engaging task, specially designed and created to effectively capture the performance of individuals with disabilities and provide a report of their performance (68).Combined intervention for different levels of motor impairment. There is a significant gap in knowledge about the benefits of combining different technologies for the rehabilitation of upper limbs, in order to increase accuracy of movement, reaction time, coincident timing and physical activity for children and adolescents with CP with different levels of gross motor function. Thus, we hope to contribute knowledge for clinical practice by examining the effects of a combined intervention on gross motor functions in individuals classified as GMFCS I-IV.Autonomic nervous system. In addition, there is another gap in knowledge concerning the adaptation of the autonomic nervous system (assessed through heart rate variability–HRV) to a combined therapy of VR and tDCS, by measuring HRV before, during, and after this intervention. Heart Rate Variability is a well-known risk marker for chronic disorders and reflects the control of autonomic nervous system in the sinus node in different health conditions, physical activity levels and exercise (70, 72, 86). HRV is impaired in individuals with CP, with a sympathetic predominance, which leads to less adaptation to physical demands (78). It characterises a cardiovascular neural profile that can lead to negative clinical results (87), such as increased cardiac arrhythmias and cardiovascular mortality (88), in addition to the risk of sudden death (86, 89), and there is evidence that maintained exercise is a feasible option to decrease cardiovascular risk in persons with sympathetic compromise (90).

Thus, we believe that the results of this study will provide scientific support for the use of combined tDCS and VR therapy in individuals with CP to improve motor skills, functionality, and the autonomic nervous system.

## Trials Status

Participant recruitment started in December 2019 and is expected to end in July 2020. Study completion is estimated by October 2020.

## Ethics Statement

The studies involving human participants were reviewed and approved by Ethical Committee of the University of São Paulo, under the number CAAE: 99577318.0.0000.5390. Written informed consent to participate in this study was provided by the participants' legal guardian/next of kin.

## Abbreviations

tDCS: transcranial direct current stimulation
VR: virtual reality
CP: cerebral palsy
mA: milliampere
HRV: heart rate variability
GMFCS: gross motor function classification system
MACS: manual ability classification system
PEDI: pediatric evaluation of disability inventory
WISC: wechsler intelligence scale for children
TRT: total reaction time.
